#### Sample size

The sample size was calculated based on the duration required to achieve the caloric goal. Because there are few studies about cyclic feeding, we referred to the studies on intermittent and continuous groups. It was assumed that the time to achieve the caloric goal would be consistent with earlier RCTs [12]: 4 days (intermittent feeding group) and 3 days (continuous feeding group). Twenty-six evaluable patients per group will provide 90% power for detection at a 5% two-sided significance level. Therefore, the total sample size will be 84. Based on the sample sizes in previous studies and an estimated dropout rate extrapolated from feasibility data of 8–10% [13], we expect that 30 patients will be enrolled in each arm and that the total sample size will be at least 90.

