## Objectives

The primary objective of the DFM-GFC study is to determine whether cyclic or intermittent feeding can extend the duration (days) of achieve caloric goal compared with continuous feeding. The secondary objective of the study is to assess whether the two feeding methods can increase the proportion of patients who achieve the caloric goal, shorten the length of stay in the ICU, and reduce the incidence of feeding complications, including the rates of onset of gastric residua and pneumonia. Abdominal pressure, motilin levels, and mortality in three groups will also be explored.

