### Statistical analysis

All statistical analyses will be performed using SPSS 20.0 software. Measurement data will be expressed as the mean ± standard deviation. Normality tests and homogeneity tests of variance will also be performed. In cases of normal distribution and homogeneity of variance, a *t* test will be conducted; otherwise, a non-parametric test will be employed. If the measurement data conform to a normal distribution, an independent sample *t* test will be applied between two groups; one-way analysis of variance (ANOVA) will be utilized between the three groups. In the case of non-normal distribution, two groups will be compared using the Mann–Whitney *U* test, and the three groups will be compared with the Kruskal–Wallis test. Enumeration data between two and three groups will be compared using chi-square/Crosstab statistical analysis, and the results will be expressed as the frequency constituent ratio (%). *P* < 0.05 will indicate statistical significance.

For patients who die or are lost to follow-up, their observation time will be censored at the time of death or date of last contact. For patients with early withdrawal who are lost to follow-up, intention-to-treat analysis (ITT) will be applied. For the second endpoint (6), cumulative proportion survival curves according to Kaplan–Meier analysis will be obtained for each group and compared with the log-rank test. To explore the group effect on the time to the event of composite outcome, with adjustment for baseline covariates, the Cox regression model will be used.

The trial will be prematurely paused or closed by the DSMB to evaluate safety information from the study or if there is evidence of harm in the study. The principal investigator (PI) will be able to access these interim results.

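### The stated 90% power at 5% covers one two-arm contrast, while the primary objective has two comparisons with continuous feeding and no stated testing order, so both figures cannot be claimed for it as written

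*Protocol article*

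**What the plan says.** - **Objectives.** The primary objective is to learn "whether cyclic or intermittent feeding can extend the duration" of reaching the caloric goal relative to continuous feeding. That is two comparisons sharing one control, and the wording is met if either succeeds.
- **Sample size.** "Twenty-six evaluable patients per group will provide 90% power for detection at a 5% two-sided significance level". The means used are 4 days (intermittent) and 3 days (continuous). On the third arm the section says only: "Because there are few studies about cyclic feeding, we referred to the studies on intermittent and continuous groups". It gives no SD and no cyclic value. It plans 30 enrolled per arm with 8–10% dropout.
- **Statistical analysis.** Two groups are compared by *t* test or Mann–Whitney, three groups by ANOVA or Kruskal–Wallis. A *P* below 0.05 "will indicate statistical significance". No test is named as primary, and pairwise tests are not made conditional on the three-group result.

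**The concern.** An unsplit 5% level and 90% power describe a single test of intermittent against continuous. The objective can be met in two ways, and the analysis section allows each pairwise test its own 5%. If the pairwise tests are read on their own, the chance of a false claim on the primary objective is above 5%. If the error is controlled, the planned pair no longer has the stated power. The cyclic comparison is half of the objective and has no power statement at all. The Discussion expects the trial to identify the best feeding method and to inform guidelines, so the error rate of the primary claim matters.

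**Working it through.** **Inputs.** From Sample size: 26 evaluable per arm, difference 1 day, two-sided 5%, 90% power, 30 enrolled per arm, 8–10% dropout. The SD is not given. The cyclic mean is not given; I use 3, 3.5 and 4 days as a range.

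**1. The plan's own figure.** Without an SD, 26 per arm can only be solved backwards.
- Normal formula: n = 2σ²(z₀.₉₇₅ + z₀.₉₀)²/δ², so σ = δ√(n/2)/(1.960 + 1.282) = √13/3.242 = 1.11 days.
- Noncentral *t*: σ = 1.09 days, used below.

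Power at 26 per arm and 5% depends strongly on this value: 94% at SD 1.0, 90% at 1.1, 84% at 1.2 and 65% at 1.5.

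**2. Familywise error without a gate.** Each contrast has variance 2σ²/n, and the shared continuous arm gives a covariance of σ²/n, so the correlation is 0.5. The chance that at least one of two tests rejects under no difference is 1 − P(|Z₁| ≤ 1.96, |Z₂| ≤ 1.96) = 9.1%. Simulated *t* tests at 26 per arm give 9.0–9.1%, and about 12% for all three pairs.

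**3. Familywise error with a gate.** If pairwise results count only after a significant ANOVA, the error is about 5% when all arms are equal. If only two arms are equal, a single true null pair remains and it is tested at 5%. With three groups the procedure therefore holds 5% throughout.

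**4. Power of the three-group test.** λ = nΣ(μᵢ − μ̄)²/σ², with σ² = 1.19.
- Means 3, 3.5, 4: λ = 26 × 0.5/1.19 = 10.9, power 83%.
- Cyclic equal to either other arm: λ = 26 × 0.667/1.19 = 14.6, power 93%.

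**5. Power for intermittent vs continuous** (simulation, normal data, SD 1.09).

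| Cyclic mean (days) | Ungated 5%, n = 26 | ANOVA gate, n = 26 | ANOVA gate, n = 27 | Holm, n = 26 |
|---|---|---|---|---|
| 3 | 90% | 88% | 89% | 84% |
| 3.5 | 90% | 83% | 84% | 84% |
| 4 | 90% | 88% | 89% | 88% |

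The n = 27 column reflects planned enrolment: 30 × 0.90 = 27 and 30 × 0.92 = 27.6 evaluable.

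**6. Power for cyclic vs continuous** at 26 per arm behind the gate, with intermittent at 4 days: 88% if the cyclic effect is 1 day, 36% if it is 0.5 day (37% ungated).

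**The case against.** The strongest reply is that the analysis section already names a three-group test. On one natural reading ANOVA or Kruskal–Wallis is the primary test and the two-group tests only follow it up. The error is then already 5%, so a 9% error is not a fact about the plan. This stands in part: the text permits that reading but does not state it. ANOVA alone also cannot say which method differs from continuous, which is what the objective asks, and its power was not the one calculated.

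A second reply is that testing order and multiplicity may sit in an analysis plan that is not shown. That is fair for the rule itself. It does not remove the mismatch inside the protocol: if that plan controls the error, the stated 90% needs restating; if it does not, the 5% does not apply to the objective.

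A reader might go further and infer that neither the 5% nor the 90% holds. The documents do not support that. Ungated tests lose the 5% but keep 90% for the planned pair (if the SD is about 1.09); controlled tests do the reverse. If both effects are 1 day, power to show at least one is above 90% even with control (about 93% behind the gate), but the protocol makes no such cyclic assumption.

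**Conclusion.** The mismatch is real and should be fixed. The sample size rests on one contrast, the objective contains two, and the analysis states no order. As written, 5% error and 90% power cannot both be claimed for the primary objective. Ungated, the error is about 9% (12% for all three pairs). Controlled by the gate, power for intermittent vs continuous is about 83–88% at 26 per arm and 84–89% at 27.

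The power figures assume normal data, an SD of 1.09 days that only the sponsor can confirm, and a cyclic mean between 3 and 4 days. The outcome is observed over 5 days, so the rank tests may be the ones used, and their power was not computed here. The results at larger SDs show sensitivity; they are not evidence that the trial is underpowered. It would also be wrong to read a flat 84% as the power of each comparison. That is the power at a 0.025 level for a 1-day effect, and no cyclic effect is stated.

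**What to change.** **Statistical analysis.** Name cyclic vs continuous and intermittent vs continuous as the two primary comparisons. State that they are interpreted only if the three-group test (ANOVA, or Kruskal–Wallis if the data are not normal) has P < 0.05. Holm across the two comparisons is an alternative.

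**Sample size.**
- State the assumed SD and its source; 26 per group implies about 1.09 days for a *t* test, to be confirmed by the sponsor.
- State the value assumed for cyclic feeding.
- Under the gate and that SD, restate power for intermittent vs continuous as about 83–88% at 26 evaluable per arm (84–89% at 27), depending on the cyclic mean. Under Holm it is about 84–88% at 26.
- Give power for cyclic vs continuous separately, for its own assumed effect: about 88% for 1 day if intermittent is also at 4 days, about 36% for 0.5 day.

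**Cost.** Wording only, no extra patients, and a slightly less favourable stated power. The article reports enrolment as ongoing, so the rule should be fixed before any comparison by arm is seen.

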**Methods:**

Different Feeding Methods on Gastrointestinal Function of Critical patients (DFM-GFC) is a randomized clinical study that will be performed to assess the effects of three feeding methods on critically ill patients. A total of 90 critically ill patients will be equally randomized into three groups: continuous feeding, cyclic feeding, and intermittent feeding. The patients will be administered a gastrointestinal nutrition preparation over 24 h via a gastric tube or over 16 h via an intermittent pump. The primary outcome is the mean duration (days) to reach the caloric goal in each group. Secondary outcomes include the rate of onset of gastric residual, abdominal pressure, the rate of onset pneumonia, and the proportion of individuals achieving the caloric goal. Additionally, the length of intensive care unit (ICU) stay and mortality rate at 28 days post-enrolment will be evaluated.

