## Methods

### Design

This is a prospective randomized controlled study. There are three parallel groups: a continuous feeding group, cyclic feeding group, and intermittent feeding group. The trial protocol was written according to the Standard Protocol Items: Recommendations for Interventional Trials Statement (SPIRIT). A SPIRIT table is provided in Fig. 1, and a SPIRIT checklist is included in Additional file 1.

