### Allocation and blinding

A random number table generated by SPSS 20.0 software (IBM Co., Armonk, NY, USA), using the randomization method, will be employed to assign the participants to each group at a ratio of 1:1:1. Patients will be enrolled during allocation according to the sequence of ICU admission. For masking, random sequences and group assignments will be sealed in opaque envelopes. As this study is a comparative assessment of treatment modalities, blinding will not be feasible. Masking related to the participant treatment arm allocation and to the treatment team for the baseline and follow-up assessments will be applied for the assessment team, data manager, and statistician.

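### The total of 84 does not follow from 26 evaluable patients per group: three groups of 26 make 78, and the step to 84 is unexplained

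*Protocol article*

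**What the plan says.** All the figures are in the Sample size section of the protocol article. The assumed times to the caloric goal are "4 days (intermittent feeding group) and 3 days (continuous feeding group"), a difference of 1 day. The requirement follows: "Twenty-six evaluable patients per group will provide 90% power for detection at a 5% two-sided significance level". The next sentence is "Therefore, the total sample size will be 84". Only then does the text bring in a drop-out estimate of 8–10%, together with the size of earlier studies, and conclude: "we expect that 30 patients will be enrolled in each arm and that the total sample size will be at least 90".

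The number of groups and the ratio are clear elsewhere. The Design section says "There are three parallel groups: a continuous feeding group, cyclic feeding group, and intermittent feeding group", and the Allocation and blinding section says that a random number table "will be employed to assign the participants to each group at a ratio of 1:1:1". The Methods part of the abstract gives the enrolment as "A total of 90 critically ill patients will be equally randomized into three groups", and the Trial status section also gives a target of 90.

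**The concern.** The word that opens the sentence on 84 presents it as the consequence of 26 evaluable patients per group. In a three-arm 1:1:1 trial it is not. Divided by three, 84 is 28 per group, a figure the article never mentions.

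The 90% power claim rests on the evaluable number. A reader who finds 26 per group and a total of 84 in consecutive sentences cannot tell whether the calculation returned 26 and the total is wrong, or returned 28 and the per-group figure is wrong. The answer decides whether 90 enrolled patients deliver the stated power after the protocol's own drop-out allowance. The article gives no standard deviation, so the reader cannot settle it by repeating the calculation.

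**Working it through.** **Inputs from the protocol article.** Three groups (Design); 1:1:1 (Allocation and blinding); 26 evaluable per group, 90% power, two-sided 5%, difference 4 − 3 = 1 day, total 84, drop-out 8–10%, 30 per arm and 90 enrolled (Sample size).

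**Step 1. The stated total.** 3 × 26 = 78. The stated 84 is 6 higher and equals 3 × 28. It is not reproduced.

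**Step 2. Is 84 equal to 78 inflated for drop-out?**
- Usual form, N/(1 − d), on the total: 78/0.92 = 84.8, rounded up to 85; 78/0.90 = 86.7, rounded up to 87.
- The same per arm: 26/0.92 = 28.3 and 26/0.90 = 28.9. Both round up to 29, so 87 in total.
- Multiplicative form, N × (1 + d): 78 × 1.08 = 84.2; 78 × 1.10 = 85.8. Per arm, 26 × 1.08 = 28.1, which gives 28 if rounded to the nearest whole number.

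Only the multiplicative form at the lowest rate, rounded down, lands on 84.

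**Step 3. Losses implied by each step.**
- 78 to 84: 1 − 78/84 = 7.1%
- 84 to 90: 1 − 84/90 = 6.7%
- 78 to 90: 1 − 78/90 = 13.3%

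None of these lies in 8–10%.

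**Step 4. What 90 enrolled delivers.** 90 × 0.92 = 82.8 and 90 × 0.90 = 81.0, so about 81–83 evaluable, or 27.0–27.6 per arm.
- Against 78: covered, with 3.0–4.8 to spare.
- Against 84: short by 1.2–3.0. Covering 84 would take 84/0.92 = 91.3 (92) to 84/0.90 = 93.3 (94) enrolled.

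**Step 5. Power.** As no standard deviation is given, I take the value that makes each candidate the 90% figure for a two-sided 5% two-sample *t* test of a 1-day difference. The normal approximation, SD = √(n/2) / (1.960 + 1.282), gives 1.11 days for n = 26 and 1.15 days for n = 28. The exact *t* calculation gives 1.09 and 1.13 days. With the *t* test:

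| Figure that carries 90% power | Implied SD (days) | Power at 26 per group | at 27 | at 28 |
|---|---|---|---|---|
| 26 per group | 1.09 | 90.0% | 91.1% | 92.1% |
| 28 per group | 1.13 | 87.7% | 88.9% | 90.0% |

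**Step 6. Would a three-group calculation give 84?** I tried one-way ANOVA with assumed SDs of 1.00, 1.09, 1.11 and 1.15 days and an assumed cyclic mean of 3, 3.5 or 4 days. Totals in equal arms ran from 63 to 105, and none was 84. An ANOVA total of 84 would in any case mean 28 per group, so it would not reconcile 84 with 26.

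**The case against.** The best defence is that 84 is already the inflated total. The text calls 26 evaluable but calls 84 only a total sample size, and that contrast suits the defence. An 8% mark-up of 78 gives 84.2, and 8% lies within the stated range. The 90 can then be read as a rounded-up minimum, since 30 per arm is also said to rest on the size of earlier studies, so the steps up to 90 need not be pure drop-out allowances. This has weight: a route to 84 within the stated range exists, and the 6.7% and 13.3% in Step 3 are not in themselves errors. But the text does not describe that route. It derives 84 directly from the evaluable number and introduces drop-out only afterwards, as a reason for 90. The route also needs the less correct form of inflation, at the lowest rate, rounded down.

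Three stronger readings are tempting, and the article does not support them.
- A reader might infer that it gives two evaluable requirements, 26 and 28 per group. It does not: 28 is only 84 divided by three, and 84 is never called evaluable.
- A reader might infer that the trial is too small. Under the only requirement stated, 26 per group, it is not.
- A reader might take the open-ended minimum of 90 as room to extend enrolment after seeing results. The Statistical analysis section does let the principal investigator see interim results, and the monitoring board may change the protocol. But no efficacy look followed by extension is planned, early stopping is tied to safety and harm, and the abstract and Trial status section give 90.

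**Conclusion.** The point holds as an arithmetic error in a stated sample-size figure: 26 per group in three equal groups is 78, and the article does not explain 84. The discrepancy is 6 patients, or 2 per arm.

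Its consequence is small and depends on which figure the calculation returned. If 26 per group is right, 90 enrolled is enough, power is about 91% at 27 evaluable per group, and only the 84 needs correcting. If 84 evaluable was the true need, the shortfall is about 1–3 patients in the whole trial and power is about 89% instead of 90%. Both power figures assume a two-sample *t* test of intermittent against continuous feeding, a 1-day difference, an SD back-calculated from the 90% claim, and 8–10% loss spread evenly over the arms. The article alone cannot show which case applies; the sponsor has to say.

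**What to change.** Replace the chain with one that reproduces, for example:

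> The calculation requires 26 evaluable patients in each of the three groups (78 in total). Allowing for 10% drop-out gives 29 per group (87), rounded up to 30 per group, 90 in total.

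If the calculation actually returned 28 per group, correct the 26 instead and restate power as about 89% for the roughly 27 evaluable patients per group that 90 enrolled will leave. In either case, check the figure against the SD used in the calculation and apply drop-out once. As a minor wording point, give the total as 90 in the Sample size section, to match the abstract and the Trial status section.

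The cost is one paragraph. Enrolment, design and analysis do not change; at most the stated power moves from 90% to about 89%.

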### Consent or assent

The patients who fulfill the study requirements will be offered a consent form consisting of the details, such as the name of the study, registered information, research background, how the study will be conducted, what the participants should do in the study, inclusion/exclusion criteria, treatment plans and obligations, putative drug-related side effects, and expenses during participation. If the patient is not conscious, his or her authorized agent or family member can provide informed consent. The patients’ personal medical data will be kept confidential. Participation in this study will be voluntary, and other treatment options will be offered to the patients who did not participate or dropped out. Informed consent will be obtained from the patients to utilize their personal and medical information in this study. To protect the privacy of the subjects, data processing will be performed anonymously, and informed consent will be obtained from each patient or statutory agent before initiation of the clinical trial.

### Data collection and management

The Second Affiliated Hospital of Guangzhou University of Chinese Medicine will be in charge of the data management and statistical analysis in this study. The clinical observations do not participate in statistical analysis. The study personnel will undergo training sessions on data collection and will be individually tested regarding data entry as well as outcome assessments before initiation of the trial. The study data will be collected and managed using SPSS 20.0. A follow-up visit or telephone follow-up will be conducted at 28 days and 12 weeks after the intervention.

An independent data safety monitoring board (DSMB) will receive the trial data from the biostatistician and choose to either continue the study as planned, change the study protocol, or stop the trial early due to harm.

The participants’ medical records will be maintained at the hospital, and the investigator, research authority, and ethics committee will be allowed access to this information. Any public report on the results of this study will not disclose the participants’ personal identities. Every effort will be made to protect the privacy of the participants’ personal medical data, according to law. Personal and medical information will be kept confidential in a safe and reliable location. At any time, the participants will be able to request access to their personal information (such as their address and contact information) and modify it if necessary.

The clinical specimen department of Guangdong Academy of Chinese Medicine will carry out the unified management and preservation of collected blood specimens. Motilin levels will be determined by ELISA at the Laboratory of Critical Care Medicine of Guangdong Academy of Chinese Medicine.

### Statistical analysis

All statistical analyses will be performed using SPSS 20.0 software. Measurement data will be expressed as the mean ± standard deviation. Normality tests and homogeneity tests of variance will also be performed. In cases of normal distribution and homogeneity of variance, a *t* test will be conducted; otherwise, a non-parametric test will be employed. If the measurement data conform to a normal distribution, an independent sample *t* test will be applied between two groups; one-way analysis of variance (ANOVA) will be utilized between the three groups. In the case of non-normal distribution, two groups will be compared using the Mann–Whitney *U* test, and the three groups will be compared with the Kruskal–Wallis test. Enumeration data between two and three groups will be compared using chi-square/Crosstab statistical analysis, and the results will be expressed as the frequency constituent ratio (%). *P* < 0.05 will indicate statistical significance.

For patients who die or are lost to follow-up, their observation time will be censored at the time of death or date of last contact. For patients with early withdrawal who are lost to follow-up, intention-to-treat analysis (ITT) will be applied. For the second endpoint (6), cumulative proportion survival curves according to Kaplan–Meier analysis will be obtained for each group and compared with the log-rank test. To explore the group effect on the time to the event of composite outcome, with adjustment for baseline covariates, the Cox regression model will be used.

The trial will be prematurely paused or closed by the DSMB to evaluate safety information from the study or if there is evidence of harm in the study. The principal investigator (PI) will be able to access these interim results.

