#### Secondary outcome

Secondary outcomes include the following: (1) the rate of onset of gastric residual (%) (defined as volume >500 mL) among the three groups; (2) abdominal pressure, (mmHg) as measured through the indirect bladder pressure, whereby the bladder urine will be emptied in the supine position, and 50 mL saline will be poured into the balloon catheter to the pubic symphysis as the base point, keeping the piezometric tube perpendicular to the ground to obtain indirect abdominal pressure; (3) the rate of onset of pneumonia in each group (%), as defined by two of the following clinical criteria, fever (> 38.3 °C) or hypothermia (≤ 36.0 °C) and leucocytosis (> 10×10^9^ cells/L) or leucopenia (≤ 4×10^9^ cells/L) and purulent tracheal aspirate or sputum. These factors are associated with the appearance of a new infiltrate or changes in the existing infiltrate on chest X-ray [11]; (4) the proportion (%) of individuals who achieve the caloric goal. The caloric goals using 25 kcal/kg (ideal body weight) for caloric need were calculated by a single nutritionist; (5) motilin levels before and 5 days after intervention; (6) the length of the ICU stay (in days) up to 12 weeks; and (7) the ICU mortality rate (%) at 28 days after intervention and survival analysis up to 12 weeks (Fig. 1). Follow-up by visit or telephone will be conducted at 28 days and 12 weeks after the intervention.

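### Deaths are censored for every endpoint and the Kaplan-Meier analysis is tied to ICU stay: the 12-week survival analysis is left with no events, or the ICU-stay curves ignore death

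*Protocol article*

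**What the plan says.** Three statements in the Statistical analysis section of the protocol article bear on this point.

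- Censoring: "For patients who die or are lost to follow-up, their observation time will be censored at the time of death" or at last contact. Death and loss to follow-up are handled alike, and the rule is not limited to any endpoint.
- Curves: "For the second endpoint (6), cumulative proportion survival curves according to Kaplan–Meier analysis will be obtained for each group", with a log-rank comparison.
- Cox model: it is to be fitted to the "time to the event of composite outcome, with adjustment for baseline covariates".

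In the list under Secondary outcome, the sixth item is "6) the length of the ICU stay (in days) up to 12 weeks". The seventh is "the ICU mortality rate (%) at 28 days after intervention and survival analysis up to 12 weeks". No composite is defined among the outcomes in the Abstract, Objectives, Primary outcome or Secondary outcome sections.

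The Abstract describes the mortality outcome differently: "mortality rate at 28 days post-enrolment will be evaluated", with no restriction to ICU deaths.

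**The concern.** A survival curve needs death as its event. Here the text makes death a censoring reason, and attaches the curves to an endpoint that is not survival. A reader cannot tell which endpoint is meant, and the rule as written fails on either reading: in one the analysis has nothing to estimate, in the other a patient who dies in the ICU is handled as though he or she would later have been discharged at the same rate as those still there.

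Deaths should be expected. Entry requires an APACHE-II score of at least 15, and the Abstract names a lower case fatality rate among the aims. At stake are the 12-week survival comparison and, on the literal reading, the ICU-stay curves. The choice between the readings would otherwise be made when the data are already in hand.

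**Working it through.** The article gives no event count, hazard ratio or power for these endpoints, so there is no planned figure to reproduce. The check follows the written rule through each reading. All hazards and mortality levels below are assumptions; only the total of 90 patients comes from the document (Sample size).

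**Reading A: (6) is a slip for (7), survival to 12 weeks.**
- If 12-week mortality were 10% to 40%, the number of deaths would be 90 × 0.10 = 9 to 90 × 0.40 = 36.
- Under the written rule each of these is censored, so events = 0 at any mortality level.
- The Kaplan-Meier curve stays at 100% in all three arms, and the log-rank statistic and a Cox hazard ratio for death are undefined.
- Changing the number from (6) to (7) does not help, because the censoring sentence still removes every event.

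**Reading B: (6) is meant, length of ICU stay.** The article names no event; take it to be discharge from the ICU alive. Assume constant cause-specific hazards, d for discharge and m for ICU death.
- One minus Kaplan-Meier with deaths censored: 1 − exp(−d·t).
- True proportion discharged alive by t: d/(d+m) × [1 − exp(−(d+m)·t)].
- True proportion dead in ICU by t: m/(d+m) × [1 − exp(−(d+m)·t)].

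Two arms, t = 28 days, d = 0.08 per day in both, m = 0.01 and 0.03 per day:

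| | m = 0.01 | m = 0.03 |
|---|---|---|
| One minus Kaplan-Meier | 1 − exp(−2.24) = 0.894 | 1 − exp(−2.24) = 0.894 |
| Discharged alive | 0.08/0.09 × (1 − exp(−2.52)) = 0.817 | 0.08/0.11 × (1 − exp(−3.08)) = 0.694 |
| Dead in ICU | 0.01/0.09 × (1 − exp(−2.52)) = 0.102 | 0.03/0.11 × (1 − exp(−3.08)) = 0.260 |

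The planned curves coincide although the second arm has about 2.5 times the ICU deaths (0.260/0.102).

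To show the range, take d = 0.1 per day and let the share of patients eventually dying in the ICU, q, run from 10% to 40%, with m = d·q/(1−q):

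| q | One minus Kaplan-Meier, day 28 | Discharged alive, day 28 | Overstatement |
|---|---|---|---|
| 10% | 0.939 | 0.860 | 0.08 |
| 20% | 0.939 | 0.776 | 0.16 |
| 30% | 0.939 | 0.687 | 0.25 |
| 40% | 0.939 | 0.594 | 0.35 |

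By day 84 one minus Kaplan-Meier is about 1.00 throughout, against 0.90 to 0.60 discharged alive, so the overstatement is 0.10 to 0.40. The size depends on the assumed hazards; the direction does not.

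**The case against.** The best defence is that this is loose wording in a condensed article. The sponsor may have meant only that observation ends at death, any statistician would code death as the event, and a zero-event analysis would be noticed at once. That may well be so, but the article does not leave the matter open. It states a censoring rule, an endpoint number and a Cox outcome, and these conflict with its own outcome list; an analysis plan that followed them would inherit the conflict. Nor does the text confine the censoring sentence to the primary outcome, which is a mean duration. The only methods named that use censoring come after that sentence, in the same paragraph.

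Several limits stand, and a reader might infer more than the document supports:

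- *That mortality cannot be compared at all.* Not so. The 28-day rate is a proportion, and the section compares counts by chi-square, which uses no censoring. Only the 12-week time-to-event analysis fails.
- *That the ICU-stay comparison is biased in favour of the arm with more deaths.* Not shown. With deaths censored, the log-rank test and Cox model compare cause-specific discharge hazards, and in the example those hazards are equal. The error lies in reading the curve as the probability of leaving the ICU alive, and in deaths not counting against an arm.
- *That both failures occur together.* They are alternatives. Under Reading A, ICU stay in days falls under the rules for measurement data (ANOVA or Kruskal–Wallis), and the competing-risk example does not apply.
- *That the 28-day clock conflicts between the Abstract and Secondary outcome.* This is weak. Primary outcome uses the phrase about days after the intervention for the first 5 days, which is the treatment course itself, so it appears to count from the start of feeding. What remains is mortality in one place and ICU mortality in the other.
- *That these are the only outcomes important to patients.* Pneumonia is also on the list.
- *That the composite outcome is a mistake.* It may be defined in a document not shown, so the text supports asking for it to be defined or deleted, and no more.

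**Conclusion.** The point holds for secondary endpoints (6) and (7); the primary outcome and the sample size do not depend on it. As written, the plan either leaves the 12-week survival analysis with no events, whatever the mortality, or produces ICU-stay curves that overstate discharge alive. The first consequence follows from the text alone. The size of the second rests on assumed constant hazards and on discharge being the event: 89% in both arms against 82% and 69% in the two-arm example, and an overstatement of 0.08 to 0.35 at day 28 over assumed ICU death shares of 10% to 40%. None of these is a forecast for this trial. Under the literal reading there is a further gap: the survival analysis listed under (7) has no log-rank test assigned to it.

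**What to change.** State event, time origin and censoring separately for each endpoint.

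1. Endpoint (7): all-cause death is the event, time runs from randomisation, and only patients alive at last contact or at 12 weeks are censored. Apply the Kaplan-Meier, log-rank and Cox analyses to this endpoint, and correct the number in the Statistical analysis section.
2. Endpoint (6): if it is analysed as time to event, use discharge from the ICU alive as the event and ICU death as a competing event, reported as cumulative incidence.
3. Define the composite outcome or delete it.
4. Reconcile mortality in the Abstract with ICU mortality under Secondary outcome.

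The cost is a few sentences. No new data are needed, because contacts at 28 days and 12 weeks are already planned. The changes should be made before outcome data by arm are examined.
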